### Primary endpoint

Levels of serum inflammatory biomarker such as; IL-6, IL-10, C-RP, Zonulin (Haptoglobulin), IL-1β, TNFα, IFNᵧ.

### Secondary endpoint

- Change in BMI
- Change in general metabolic indicators such as fasting blood glucose
- Changes in blood-based markers relevant to MASLD (e.g., CK18-M30, CK18-M65, PROC3, Enhanced Liver Fibrosis (ELF), NIS2+™, YKL-40, microRNA miR-34a-5p, liver-associated enzymes such as Alanine Aminotransferase (ALT), Aspartate Aminotransferase (AST), gamma-glutamyl transferase (GGT), Alkaline Phosphatase (ALP)), bilirubin levels, lipid profiles, and platelet counts.
- Gut microbiome: changes in composition
- Change in non-invasive physiological assessments linked to liver characteristics: FibroScan™ CAP value and Liver stiffness based on vibration-controlled transient elastography (VCTE)
- Change in liver fat and other surrounding abdominal organs fat through alterations in Dixon MRI sequence
- Alterations in T2* MRI measures of intestinal permeability

### Stopping rules and discontinuation

Since the current study is a dietary intervention, research team do not foresee any adverse events. However, if a participant develops a severe adverse reaction following consumption of the supplement (i.e. severe bloating amongst those who have a low habitual intake of dietary fibre), they will be asked to contact the study team immediately. Based on the severity of the event and at the discretion of the CI, the study team may advise the participant to continue or withdraw from the study.

Moreover, participants who will agree to have MRI scans, will be carefully monitored during the scan and if their medical or physiological status alter rapidly, then it may be necessary to stop scanning based on the radiologist advice.

Participants may withdraw from the study at any point. Significant non-compliance with the study schedule may lead to a participant being withdrawn from the study.

## RANDOMIZATION AND BLINDING

The study will be a parallel design, placebo controlled, randomised intervention study in which participants will be allocated to either the intervention or placebo arm. The randomisation will be done through an online software (sealedenvelope.com) to determine intervention A or B at enrolment.

One of research team will be un-blinded and will be responsible for preparing and labelling of the intervention/placebo as either A or B based on random selection using an online software (sealedenvelope.com). A or B – pectin will be assigned to the arm in the first envelope. This information will be securely documented in a new sealed enveloped stored in the chief investigators locked desk. All other members of the team will be blinded to the assignment of A or B as the intervention.

This will be unblinded once the study is complete after the sample analysis and data analysis is complete.

### Maintenance of randomisation codes and procedures for breaking code

The assignment of pectin as intervention A or B will be documented in a sealed envelope in the CI’s desk. This can be accessed and broken, if necessary, on direction of the CI in the event of any serious adverse event.

## TRIAL/STUDY MANAGEMENT

The CI has overall responsibility for the study and shall oversee all study management.

The data custodian will be the Chief Investigator.

The study will form part of PhD project undertaken by [name] registered at the University of Nottingham (UoN) whose role will include responsibility for recruiting and consenting patients and collecting data. The PhD student will be responsible for arranging and conducting study visits, analysing samples and analysing the data. The student will comply with University of Nottingham policies and regulations.

## DURATION OF THE TRIAL / STUDY AND PARTICIPANT INVOLVEMENT

Study Duration: 24 Months.

Recruitment: 22 months.

Follow up: 1.5 months.

The study is projected to have a total duration of 24 months from the start date.

Participant Duration:

6 weeks (+/- 5 days)

### End of the Trial

The end of the study will be the date of the last visit of the last participant or the completion of all follow-up monitoring, data collection, and required tissue sample analysis for the study participants, whichever is later..

## SELECTION AND WITHDRAWAL OF PARTICIPANTS

###

### Recruitment of patients for the study

The study will be set in secondary care at Nottingham University Hospitals NHS Trust through partnership with the University of Nottingham BRC.

Participants will be recruited through:

- Advertisements through posters, social media platforms and local websites:

Patient posters containing study information will be advertised in areas of the University and in the relevant clinical areas at Nottingham University Hospitals NHS Trust such as the Hepatology Department. Moreover, study will be advertised through University of Nottingham and NIHR Nottingham Biomedical Research Centre –local websites and social media platforms using the same patient posters. Study team will directly contact individuals who express interest in participating in the study.

- Approaching patients at hepatology clinics:

Participants will also be recruited from hepatology clinics. The initial approach will be from a member of the patient’s usual care team (which may include the investigator). Information about the trial will be on display in the relevant clinical areas.

The investigator or their nominee, e.g. from the research team or a member of the participant’s usual care team, will inform the participant of all aspects pertaining to participation in the study.

- Approaching participants with NAFLD/MASLD diagnosis who previously participated in research studies where [name] was the CI and who have consented to be contacted for future research.

Designated members of the study team will contact past research participants using contact details previously provided or obtained by the CI from patient records, to invite them to participate in this study.

It will be explained to the potential participant that entry into the trial is entirely voluntary and that their treatment and care will not be affected by their decision. It will also be explained that they can withdraw at any time, but attempts will be made to avoid this occurrence. In the event of their withdrawal, it will be explained that their data collected so far cannot be erased and we will seek consent to use the data in the final analyses where appropriate.

### Recruitment of healthy volunteers

A research team from the University of Nottingham has developed an MRI protocol to assess intestinal wall thickness to indicate gut permeability on healthy participants [17]. To validate this tool to be used on MASLD patients, our team will scan 15 healthy volunteers twice, at baseline and after 6 weeks, and then compare their results with MASLD patients’ results at baseline and after 6 weeks. Participants will be recruited through:

- Approaching healthy participants, with CAP<250 kpa<8kP by a FibroScan™ within the past 6 months, who previously participated in research studies where [name] was the CI and who have consented to be contacted for future research. Designated members of the study team will contact past research participants using contact details previously provided or obtained by the CI from patient records, to invite them to participate in this study.

### Eligibility criteria

### Inclusion criteria for the main study

- Patients with clinical diagnosis of MASLD, having assessment suggesting that liver fat > 5% (e.g. histological evidence or/ and Transient Elastography using CAP- FibroScan™ in the past month and/or liver imaging (such as CT or magnetic resonance imaging MRI)).
- Participants willing and able to give informed consent for participation in the study.
- Participants aged ≥18 years who have a body mass index (BMI) between 18.5 and 39.9 kg/m^2^ and stable weight (weight gain or loss ≤ 3kg) for the past 3 months.
- For diabetic participants: controlled blood glucose levels Haemoglobin A1C (HbA1c) <7.0% (<53 mmol/mol) [1].
- Able to undergo CAP-FibroScan™.

**Inclusion criteria for healthy participants who will have MRI scans:**

- Participants willing and able to give informed consent for participation in the study.
- Participants aged ≥18 years.
- participants with CAP<250 kpa<8kP by a FibroScan™ within the past 6 months.

### Exclusion criteria for the main study

- Have allergy toward soya, milk or chocolate.
- Have allergy toward pectin.
- Participants on a vegan diet.
- Have eating disorders or difficulties or gastrointestinal conditions e.g. malabsorptive conditions such as coeliac, irritable bowel syndrome (IBS) or Inflammatory Bowel Disease (IBD) or gastroparesis.
- Have chronic malnutrition condition.
- History of major surgery which potentially limits participation or completion of the study.
- History of previous intestinal surgery known to affect food intake
- or digestive function, including bariatric surgery.
- Use of antibiotics, antifungal medications, probiotics or prebiotics 90 days before the start of the study.
- Are taking the following medications: immunosuppressants, amiodarone and/or perhexiline.
- Are currently following or anticipated to commence a specialised commercially available weight loss diet and/or program or concomitant use of any weight loss medication or herbal weight loss products.
- History of side effects towards probiotics or prebiotics.
- History or current psychiatric illness.
- History or current neurological condition (e.g. epilepsy).
- Participants with other liver abnormalities.
- Evidence of monogenic metabolism diseases such as Lysosomal acid lipase deficiency (LALD), Wilson disease, Hypobetalipoproteinemia, or inborn errors of metabolism.
- Have had a weight change exceeding 3 kg within 3 months.
- Uncontrolled diabetes, active malignancy, or chronic infections.
- Having symptoms of active infection.
- Excessive alcohol intake defined as self-reported intakes greater than 21 units per week in men, and 14 units per week in women.
- Participants who are pregnant, breast feeding or actively planning pregnancy will be excluded from the study.
- Participation in any other trial in the last 3 months.

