| Eligibility criteria | **Inclusion criteria for the main study:**  -Patients with clinical diagnosis of MASLD (formerly termed non-alcoholic fatty liver disease (NAFLD)), having assessment suggesting that liver fat > 5% (e.g. histological evidence or/ and Transient Elastography using Controlled Attenuation Parameter (CAP)- FibroScan™ in the past month and/or liver imaging (such as ultrasound, computerized tomography (CT) or magnetic resonance imaging (MRI)).  -Participants willing and able to give informed consent for participation in the study.  -Participants aged ≥18 years who have a body mass index (BMI) between 18.5 and 39.9 kg/m^2^ and stable weight (weight gain or loss ≤ 3kg) for the past 3 months.  -For diabetic participants: controlled blood glucose levels Haemoglobin A1C (HbA1c) <7.0% (<53 mmol/mol) [1].  -Able to undergo CAP-FibroScan™.  **Inclusion criteria for healthy participants who will have MRI scans:**  -Participants willing and able to give informed consent for participation in the study.  -Participants aged ≥18 years.  - participants with CAP<250 kpa<8kP by a FibroScan™ within the past 6 months.  **Exclusion criteria for the main study:**  -Have allergy toward soya, milk or chocolate.  -Have allergy toward pectin.  -Participants on vegan diet.  -Have eating disorders or difficulties or gastrointestinal conditions e.g. malabsorptive conditions such as coeliac, Irritable Bowel Syndrome (IBS) or Inflammatory Bowel Disease (IBD) or gastroparesis.  -Have chronic malnutrition condition.  -History of major surgery which potentially limits participation or completion of the study.  -History of previous intestinal surgery known to affect food intake  or digestive function, including bariatric surgery.  -Use of antibiotics, antifungal medications, probiotics or prebiotics 90 days before the start of the study.  -Are taking the following medications: immunosuppressants, amiodarone and/or perhexiline.  -Are currently following or anticipated to commence a specialised commercially available weight loss diet and/or program or concomitant use of any weight loss medication or herbal weight loss products.  -History of side effects towards probiotics or prebiotics.  -History or current psychiatric illness.  -History or current neurological condition (e.g. epilepsy).  -Participants with other liver abnormalities.  -Evidence of monogenic metabolism diseases such as Lysosomal acid lipase deficiency (LALD), Wilson disease, Hypobetalipoproteinemia, or inborn errors of metabolism.  -Have had a weight change exceeding 3 kg within 3 months.  -Uncontrolled diabetes, active malignancy, or chronic infections.  -Having symptoms of active infection.  - Excessive alcohol intake defined as self-reported intakes greater than 21 units per week in men, and 14 units per week in women.  -Participants who are pregnant, breast feeding or actively planning pregnancy will be excluded from the study.  -Participation in any other trial in the last 3 months.  **Exclusion criteria for healthy volunteers MRI scans and patients optional MRI scans:**  -Contraindications for MRI scanning: having pacemakers, defibrillators, neurostimulators, prohibited medical implants, and foreign bodies (e.g. bullets, shrapnel, metal slivers), history of metallic foreign body in eye(s) and penetrating eye injury that could present a risk during an MRI scan.  -Difficulty breathing or inability to lie flat, as well as conditions that could worsen under stress (such as anxiety or panic disorders, claustrophobia, uncontrolled hypertension, or seizure disorders) severe enough to prevent undergoing an MRI.  -Contraindications to Hyoscine butylbromide (Buscopan®): Previous adverse drug reaction (allergic, hypersensitivity or other), Angle-closure glaucoma, tachycardia, ischaemic heart disease, myasthenia gravis, prostatic enlargement with urinary retention requiring catheterisation, mechanical stenosis in the gastrointestinal tract, paralytic or obstructive ileus, hypotension, cardiac disease, recent heart attack or any arrhythmias, thyrotoxicosis, gastro-oesophageal reflux disease, hiatus hernia, ulcerative colitis. |

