**Known Side Effects**

As this is a dietary intervention trial using widely available foodstuffs consumed as advised by manufacturers, no serious adverse events/side-effects or ethical issues are expected. Participants will be given the details of the trial supplements - those with food allergies or sensitivities to components of the foods/components will not be recruited. Increasing fibre intake may result in bloating amongst those who have a low habitual intake of dietary fibre. However, such effects are mild and not considered as a safety concern. Presence of inflammatory bowel disease, irritable bowel syndrome, and gastrointestinal resection surgery are exclusion criteria for the study to avoid exacerbating these conditions. Pregnant and breastfeeding women will be excluded from the study because there is limited data regarding the safety of pectin and whey protein consumption during pregnancy and breastfeeding.

The common side effect from administration of the Buscopan® (that will be used during MRI scans as antispasmodics) are very short lived (blurred vision and raised heart rate) and participants will be advised to stay at the test centre until their vision returns to normal (this normally occurs within 30 minutes of the injection). Rare side effects from administration of the Buscopan® injection include skin reactions, tachycardia, dry mouth, dyshidrosis, and in extremely rare cases angle-closure glaucoma. This will be monitored throughout the study visit at Sir Peter Mansfield Imaging Centre (SPMIC) by a registered medical doctor who will be a member of the research team and who will administer Buscopan® and monitor participants.

Mannitol 2.5% / Locust bean gum 0.2% will be used during MRI scans as oral contrast. Mannitol increases MRI contrast between the lumen and the bowel wall, and the addition of locust bean gum serves to counteract some of the recognised side effects associated with Mannitol ingestion, which can include flatulence and alteration of gastrointestinal microbiota leading to bowel spasms and diarrhoea.

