### Assessment of safety

This study is not aimed at primarily assessing safety as the study is a dietary intervention using components sourced from common foods, research team foresee no adverse reaction or side effects. Increasing fibre intake may result in bloating amongst those who have a low habitual intake of dietary fibre. However, such effects are mild and not considered as a safety concern. Those reporting having inflammatory bowel disease, those who experience irritable bowel syndrome, and those having had gastrointestinal resection surgery will not be recruited. Moreover, those with food allergies or sensitivities to components of the investigational products will not be recruited.

Pregnant and breastfeeding women will be excluded from the study because there is limited data regarding the safety of pectin and whey protein consumption during on pregnancy and breastfeeding.

The common side effect from administration of the Buscopan® (that will be used during MRI scans as antispasmodics) are very short lived (blurred vision and raised heart rate) and participants will be advised to stay at the test centre until their vision returns to normal (this normally occurs within 30 minutes of the injection). Rare side effects from administration of the Buscopan® injection include skin reactions, tachycardia, dry mouth, dyshidrosis, and in extremely rare cases angle-closure glaucoma. This will be monitored throughout the study visit at Sir Peter Mansfield Imaging Centre (SPMIC) by a registered medical doctor who will be a member of the research team and who will administer Buscopan® and monitor participants.

Mannitol 2.5% / Locust bean gum 0.2% will be used during MRI scans as oral contrast. Mannitol increases MRI contrast between the lumen and the bowel wall, and the addition of locust bean gum serves to counteract some of the recognised side effects associated with Mannitol ingestion, which can include flatulence and alteration of gastrointestinal microbiota leading to bowel spasms and diarrhoea.

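### The exclusion list is narrower than the safety text on supplement allergy, supplement sensitivity and gastrointestinal resection

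*Protocol*

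**What the plan says.** Known Side Effects says that "those with food allergies or sensitivities to components of the foods/components will not be recruited". It goes on: "Presence of inflammatory bowel disease, irritable bowel syndrome, and gastrointestinal resection surgery are exclusion criteria for the study". Assessment of safety, under Statistics, makes the same two commitments: "those with food allergies or sensitivities to components of the investigational products will not be recruited", and "those having had gastrointestinal resection surgery will not be recruited". None of these statements carries a qualifier.

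The exclusion list, in Exclusion criteria for the main study and again in the Synopsis, has these related items:

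- Two allergy items: "Have allergy toward soya, milk or chocolate" and "Have allergy toward pectin".
- One item on earlier reactions: "History of side effects towards probiotics or prebiotics".
- One intestinal surgery item: "History of previous intestinal surgery known to affect food intake", which continues to digestive function and includes bariatric surgery.
- A major surgery item, limited to surgery that might stop someone taking part or finishing.
- An item on eating difficulties and gastrointestinal conditions, which names irritable bowel syndrome and inflammatory bowel disease among its examples.

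**The concern.** The list that decides eligibility and the text that describes the safety protections disagree about who may enter. The safety sections expect no serious events (Known Side Effects) or no adverse reactions (Assessment of safety), and both point to these exclusions. A reader of either section would believe in protections that the list does not contain.

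It could also matter at screening. Under Trial / Study Intervention and Regimen, eligibility is checked against a checklist, and when medical notes are unavailable it rests on participants' own answers about their medicines and conditions. If the checklist follows the exclusion list, nobody need ask about an item the list lacks. Staff would also have no rule for whether enrolling such a person is a protocol deviation.

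**Working it through.** No calculation in the plan is at issue. The check compares the safety text with the list, and then with the ingredients.

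**Text against list**

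| Subject | Known Side Effects and Assessment of safety | Exclusion list (main section and Synopsis) |
| --- | --- | --- |
| Allergy | Any supplement component | Soya, milk, chocolate and pectin only |
| Sensitivity | Any supplement component | No item; the nearest concerns probiotics and prebiotics |
| Gastrointestinal resection | Excluded, unqualified | Only intestinal surgery with a known effect on eating or digestion, or major surgery that might limit taking part |
| Irritable and inflammatory bowel disease | Excluded | Excluded by name |

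The last row is a useful control. Known Side Effects names three gut exclusions in one sentence. Two of the three appear by name in the list; resection does not.

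**List against ingredients.** Details of Product(s) describes the pectin, the cocoa powder and the whey powder. Counting each ingredient once, and vitamins C and D together:

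- Reached by a named allergen: pectin, cocoa, soya lecithin, whey isolate (milk) = 4.
- Not reached: cinnamon, natural flavouring, sunflower lecithin = 3.
- Given no weight here: sugar, salt, vitamins = 3.
- Total: 4 + 3 + 3 = 10.

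The three that are not reached come from the cocoa and whey powders, so both arms receive them. The pectin specification also allows sulphur dioxide up to 50 mg/kg. Counting it would raise the unreached number to 4, in the pectin arm only, at no more than 0.015 kg × 50 mg/kg = 0.75 mg per daily dose.

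**Sensitivity.** The probiotic and prebiotic item could at most reach the pectin. It does not reach whey, cocoa, cinnamon or sunflower lecithin. Nor can allergy simply be read to include sensitivity: both safety sections name the two separately, and the MRI exclusions for Buscopan spell out allergic, hypersensitivity and other reactions.

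**Who passes the list but is barred by the safety text.** Three examples are a person with a cinnamon or sunflower allergy, a person with a milk sensitivity that is neither an allergy nor a gastrointestinal condition, and a person with a past resection, no known functional effect and no other excluding condition.

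**The case against.** The best reply is that this is silence more than contradiction. The safety sections are current protocol text and bar these people outright. The list nowhere says they may enter and does not claim to be exhaustive, so the protocol read as a whole excludes them. Participants are also given the supplement details, which lets them identify an ingredient they react to. That reading is fair for allergy and sensitivity, and it softens the point. It does not work for resection, which Known Side Effects calls an exclusion criterion although the list has no such criterion. It also asks screening staff to gather eligibility rules from sections on side effects and statistics.

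A second reply is that other items catch most of these people. The gastrointestinal conditions item is open-ended and could take in some milk sensitivity. The two surgery items cover many resections. Exposure to lactose is small: whey has 1.7 g sugars per 100 g, so whey sugars are 30 × 0.017 = 0.51 g/day in the control arm and 15 × 0.017 = 0.255 g/day in the pectin arm. All of this stands and makes the gap narrow. It does not close it: none of these items names component sensitivity or resection, and the lactose figure says nothing about sensitivity to milk protein.

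Third, the practical consequence is uncertain. The screening checklist is not shown and may be wider than the list, and weekly calls record adverse events. That also stands. The ingredient count depends on what one counts as an ingredient and only illustrates the mismatch, which rests on the wording.

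**Conclusion.** The concern holds as a minor internal inconsistency. The safety text states exclusions that the list does not contain: allergy to any component, sensitivity to any component, and gastrointestinal resection without qualification. At least 3 of the 10 ingredients counted fall outside the named allergens, and 1 of the 3 gut exclusions in Known Side Effects has no matching item.

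The number of people affected is probably very small, but the protocol gives no prevalence, so this is a judgement. The mismatch in wording is certain. Whether it would let anyone in depends on the screening checklist following the list, which cannot be verified. Sample size, power and the primary analysis are not affected.

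**What to change.** In the Synopsis and in Exclusion criteria for the main study, replace the two allergy items with one: allergy or sensitivity to any component of the study supplements, including soya, milk or whey, cocoa, cinnamon, sunflower lecithin and pectin. Add previous gastrointestinal resection surgery as its own item. Carry both into the screening checklist.

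If the narrower list is what the sponsor intended, leave it and correct Known Side Effects and Assessment of safety to match.

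The cost is two lines in one amendment, one or two questions at screening, and an occasional extra screen failure.
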